## Abstract

**Background:**

Food insecurity, or the lack of consistent access to nutritionally adequate and safe foods, effects up to 50% of people living with HIV (PWH) in the United States (US). PWH who are food insecure have lower antiretroviral adherence, are less likely to achieve viral suppression, and are at increased risk developing of serious illnesses, including cardiometabolic comorbidities. The objectives of this study are to better understand how food insecurity contributes to the development of cardiometabolic comorbidities among PWH and to test a novel bilingual peer navigation-mHealth intervention (weCare/Secure) designed to reduce these comorbidities in food-insecure PWH with prediabetes or Type 2 diabetes (T2DM).

**Methods:**

In Aim 1, we will recruit a longitudinal cohort of 1800 adult (≥18 years) PWH from our clinic-based population to determine the difference in the prevalence and incidence of cardiometabolic comorbidities between food-secure and food-insecure PWH. Food insecurity screening, indicators of cardiometabolic comorbidities, and other characteristics documented in the electronic health record (EHR) will be collected annually for up to 3 years from this cohort. In Aim 2, we will conduct a randomized controlled trial among a sample of food-insecure PWH who have prediabetes or T2DM to compare changes in insulin sensitivity over 6 months between participants in weCare/Secure and participants receiving usual care. In Aim 3, we will conduct semi-structured individual in-depth interviews to explore the effect of the intervention among intervention participants with varying insulin sensitivity outcomes.

**Trial status:**

Aim 1 (longitudinal cohort) recruitment began in May 2022 and is ongoing. Aim 2 (intervention) recruitment is planned for spring 2023 and is expected to be completed in spring 2024. Aim 3 (process evaluation) data collection will occur after sufficient completion of the 6-month assessment in Aim 2. Final results are anticipated in fall 2025.

**Conclusions:**

This research seeks to advance our understanding of how food insecurity impacts the development of cardiometabolic comorbidities among PWH and how food insecurity interventions may alleviate relevant comorbidities. Given the growing interest among health systems in addressing food insecurity, if the intervention is found to be efficacious, it could be broadly disseminated across HIV clinical care settings.

**Trial registration:**

ClinicalTrials.gov NCT04943861. Registered on June 29, 2021.

The social determinants of health (SDH), or the circumstances in which people are born, work, live, and age, have a profound impact on morbidity and mortality [1–5]. SDH can negatively affect health by leading to adverse social risk factors such as food insecurity, or the lack of consistent access to nutritionally adequate and safe foods. In 2021, 10.2% of United States (US) households, or over 30 million people, were food insecure, and nearly 90% of the US counties with the highest rates of food insecurity were in the South [6], particularly affecting people living in rural communities [7–9]. Compared to food-secure individuals, food-insecure individuals are more likely to have worse diet quality, higher smoking rates, and less physical activity, and food insecurity is associated with type 2 diabetes mellitus (T2DM), hypertension, and cardiovascular disease [10–14]. Existing research describes factors influencing food insecurity and cardiometabolic comorbidities through the pathways outlined in Fig. 1: nutritional, mental health, and behavioral [15, 16].

**Fig. 1 Fig1:**
[figure not shown]
Food insecurity co-morbidity conceptual model

People living with HIV (PWH) are particularly at risk for the detrimental effects of food insecurity; up to 50% of PWH in the US are estimated to be food insecure [11–13]. PWH who are food insecure have lower antiretroviral adherence, are less likely to achieve viral suppression, and have an increased incidence of serious illnesses and mortality [12, 17–19].

Although food insecurity is associated with cardiometabolic comorbidities in people without HIV, little is known about how food insecurity affects the development of these comorbidities among PWH [20–22]. At the same time, there is a critical need for interventions to reduce food insecurity among PWH. Many national healthcare organizations, including the National Academy of Medicine, recommend that clinicians and health systems identify and address food insecurity as part of routine clinical care [23–25]. Interventions are being implemented to address food insecurity in primary care settings [26–28], but there are few evidence-based interventions in clinical settings caring for PWH [13, 26–28]. An effective strategy to address food insecurity in PWH could be disseminated broadly across clinics and health systems to improve the care and health of PWH.

Peer navigation to support access to food has the potential to reduce cardiometabolic risk through reducing food insecurity among PWH. Natural helping (e.g., peer navigation, lay health advising, and peer support) is gaining attention as a strategy to improve health outcomes in underserved or vulnerable communities [29–44], and the strategy holds particular promise for reducing cardiometabolic risk among PWH. Peer navigation differs from patient or clinic-based navigation; peer navigators share a unique understanding of the population they are working with, based on shared experiences and/or sociodemographic characteristics. Additionally, mHealth is a powerful tool for peer navigators to use with PWH. Social media use, including Facebook, Instagram, texting, and GPS-based mobile applications (“apps”) designed for social and sexual networking, have been increasing in the US, due in part to the proliferation of mobile devices [45–48]. PWH are often socially and geographically isolated [49, 50], making mHealth approaches that utilize social media a useful strategy for reaching PWH and providing peer navigation. mHealth can shrink the distance between individuals needing support and those who can provide support.

Accordingly, the objectives of this study are to better understand how food insecurity contributes to the development of cardiometabolic comorbidities among PWH and to test a novel bilingual peer navigation-mHealth food insecurity intervention (weCare/Secure) designed to reduce these comorbidities among food-insecure PWH living in the southeastern United States.

## Methods

### Ethics statement

The Institutional Review Board (IRB) at the Wake Forest University School of Medicine is the IRB of record. The Wake Forest University School of Medicine IRB has reviewed and approved all the procedures outlined in this protocol. The study is registered with ClinicalTrials.gov (NCT04943861).

### Study settings

This protocol is being implemented at the Wake Forest Infectious Diseases Specialty Clinic, a clinic within an academic medical center that provides HIV medical care for over 2000 patients with multiple comorbidities and significant psychosocial complexity annually. The population consists of a mix of uninsured patients and patients with private and public insurance (e.g., Medicaid). The clinical catchment area includes a 40-county area of largely rural North Carolina, Virginia, West Virginia, and Tennessee. The clinic is comprised of PWH from particularly marginalized communities; 67% are African American/Black; 9% are Latine; 50% are 50 years old or older; 35% are uninsured; and many are low income and have limited educational attainment.

### Overall study design

The objective of this study is to better understand the relationship between food insecurity and cardiometabolic comorbidities and to test the effect of a food insecurity intervention (weCare/Secure) on insulin sensitivity among PWH with prediabetes or T2DM. In Aim 1, we will recruit a longitudinal cohort of 1800 from our clinic-based population of adult PWH to determine the difference in the prevalence and incidence of cardiometabolic comorbidities between food-secure and food-insecure PWH (Fig. 2).

**Fig. 2 Fig2:**
[figure not shown]
Overall study design for food insecurity and cardiometabolic comorbidities among persons living with HIV

Food insecurity screening, indicators of cardiometabolic comorbidities, and other characteristics documented in the electronic health record (EHR) will be collected annually for up to 3 years from this cohort. In Aim 2, we will conduct a randomized controlled trial (RCT) among a sample of food-insecure PWH who have prediabetes or T2DM to compare changes in insulin sensitivity over 6 months between participants in weCare/Secure and participants receiving usual care. In Aim 3, we will conduct semi-structured individual in-depth interviews to understand the effect of the intervention on insulin sensitivity among intervention participants.

#### Aim 1: Use a longitudinal cohort to determine the difference in the prevalence and incidence of cardiometabolic comorbidities between food-secure and food-insecure PWH

##### Participants

To be eligible to participate in Aim 1, a participant must (a) be a patient of the Wake Forest Infectious Diseases Specialty Clinic, (b) be living with HIV, (c) be ≥18 years of age, and (d) provide informed consent. PWH will be excluded if they are unable to speak English or Spanish or have cognitive impairment that would prevent participation. Aim 1 participants will be compensated $20 at each data collection period.

##### Data collection

For this aim, we will recruit, enroll, and collect data from a longitudinal cohort of PWH (*N* = 1800); data will be collected at baseline and at 12-, 24-, and 36-month follow-up. We will implement the Mobile Patient Technology for Health (mPATH™) in the clinic. mPATH™ is a patient-facing digital health platform allowing patients to confidentially answer routine ambulatory screening questions [51]. At the time of ambulatory visit check-in, patients are provided a tablet by front desk staff with mPATH™ that includes standard clinic assessments of fall risk, depression, and anxiety, and incorporates the 2-item Hunger Vital Sign measure [52, 53], which measures household food insecurity over the prior 12 months. Because people at risk of food insecurity often have other unmet social needs, mPATH™ also assesses housing stability and transportation barriers (Table 1) [54]. The mPATH™ platform offers data collection in English or Spanish. If a participant is unable to effectively utilize mPATH™, a clinic staff member will assist by reading the items to the participant. Data from mPATH™ flows directly into the participant’s EHR.

**Table 1 Tab1:** Study measures

Domain	Measures and citations	Data source
*Aim 1 and Aim 2*		
Prediabetes or T2DM (primary outcome)	Fasting and non-fasting glucose, A1C level, diagnosis codes (ICD-10), current diabetic medications (including glucagon-like peptide 1 agonist, sodium-glucose cotransporter 2 inhibitor, dipeptidyl peptidase 4 inhibitor, sulfonylurea, incretin mimetic, or insulin)	EHR data extraction (baseline, 12mo, 24mo, 36mo)
Hypertension, hyperlipidemia, obesity, and elevated waist circumference (secondary outcomes)	History of high blood pressure, current blood pressure-lowering medications, 3 most recent systolic and diastolic blood pressure readings, history of high cholesterol, current cholesterol-lowering medications, lipid panel (total, LDL, HDL, triglycerides), body-mass index, waist circumference	EHR data extraction (baseline, 12mo, 24mo, 36mo)
Food insecurity	2-item Hunger Vital Sign [50, 51]	EHR data extraction (baseline, 12mo, 24mo, 36mo)
Basic demographics	Age, race, ethnicity, gender, sexual orientation, insurance status, preferred language, zip codes	EHR data extraction (baseline, 12mo, 24mo, 36mo)
Health status	Time since HIV diagnosis and since ART initiation, current HIV medications (including ART), other relevant medications (e.g., oral corticosteroids), pregnancy status, smoking status, other medical histories	EHR data extraction (baseline, 12mo, 24mo, 36mo)
Other unmet social needs	Housing stability, transportation barriers to obtaining medical care or medications	EHR data extraction (baseline, 12mo, 24mo, 36mo)
*Aim 2*		
Insulin sensitivity (primary outcome)	Homeostatic model assessment of insulin resistance (HOMA-IR)	EHR data extraction (baseline and 6 months)
Past 30-day food insecurity	USDA Food Security Survey Module (FFSM)	Quantitative assessment (baseline and 6 months)
Socioeconomic characteristics	Educational attainment, marital status, household composition and size, employment status, income, ratio of household income to poverty	Quantitative assessment (baseline only)
*Nutritional pathway*		
Use of food resources	Seeking a community-based food resource (e.g., food bank or pantry), applying for or receiving Supplemental Nutrition Assistance Program (SNAP), Special Supplemental Nutrition Program for Women, Infants, and Children (WIC), and Temporary Assistance for Needy Families (TANF) benefits	Quantitative assessment (baseline and 6 months)
Food expenditures	Out-of-pocket monthly food expenditures [55]	Quantitative assessment (baseline and 6 months)
Diet quality	Daily fruit and vegetable intake [56]	Quantitative assessment (baseline and 6 months)
Nutrition knowledge	Food literacy [57]	Quantitative assessment (baseline and 6 months)
*Mental health pathway*		
Mental health challenges	Anxiety/stress, depression, substance use [2];\, social support [58]	Quantitative assessment (baseline and 6 months)
Stigma	Internalized stigma related to food insecurity, sexual or gender identity, and/or HIV	Quantitative assessment (baseline and 6 months)
Self-efficacy	Self-efficacy to address food insecurity, manage cardiometabolic comorbidities, and/or engage in HIV care	Quantitative assessment (baseline and 6 months)
*Behavioral pathway*		
Diabetes care	Diabetes self-care activities [59, 60], diabetes self-efficacy [59, 61]	Quantitative assessment (baseline and 6 months)
HIV care engagement	Missed appointments, viral load, medication adherence	EHR data extraction & quantitative assessment (baseline and 6 months)

Data for this aim will be extracted from the EHR, as summarized in Table 1. The primary outcome for Aim 1 is prediabetes or T2DM. A participant will be considered to have a clinical diagnosis of prediabetes if they have a hemoglobin A1C level ≥ 5.7% and < 6.5% measured at the time of the clinic visit. A participant will be determined to have T2DM if they have any one of the following: an A1C ≥ 6.5%, a prior history of T2DM based on ICD-10 codes in the EHR, and/or currently taking a diabetic medication (including glucagon-like peptide 1 receptor agonist, sodium-glucose cotransporter 2 inhibitor, dipeptidyl peptidase 4 inhibitor, sulfonylurea, incretin mimetic, or insulin).

##### Power and sample size for Aim 1

We anticipate accruing 1800 patients (~ 90% of the clinic population) to complete the baseline assessment. These participants will be followed for up to 3 years with an expected loss to follow-up of 15%. Rates of food insecurity in the overall population in our region are 15–20%. In our previous weCare study, about 27% of participants needed support services for food in the past 6 months; in addition, 57% of the clinic population is below 100% of the federal poverty level. Therefore, we assume that 30% of this sample will be food insecure (*n*=540). Based on available data of PWH [55], we expect the baseline prevalence of prediabetes/T2DM in the food-secure group to be 25% at baseline. Under these assumptions, we will have 80% power to detect a difference between a baseline prevalence of prediabetes/T2DM of 25% among non-food-insecure participants and a prevalence of 31.6% (odds ratio=1.38) among food-insecure participants using a two group *χ*^2^ test with a 5% two-sided significance level. Assuming that 75% of the sample will not have prediabetes/T2DM at baseline, the sample size for estimating incidence is *n* = 1350. Based on a study by Nansseu et al. of PWH, we assume the incidence of prediabetes is 125 per 1000 person-years and the incidence of T2DM is 13.7 per 1000 person-years [56]. We then have 80% power to detect a prediabetes incidence rate ratio of 1.7 between those with and without food insecurity and a T2DM incidence rate ratio of 3.7, using a log-rank test for two survival curves with a 5% two-sided significance level.

##### Analysis plan for Aim 1

First, we will compare characteristics of food-secure and food-insecure participants using *t*-tests for continuous covariates and *χ*^2^ tests for discrete covariates. Next, we will estimate the prevalence of prediabetes and T2DM in each group. To compare the unadjusted prevalence of prediabetes and T2DM at baseline for food-secure and food-insecure participants, we will conduct a two-group *χ*^2^ test for two proportions with a 5% two-sided significance level. We will use logistic regression modeling to estimate the association between food insecurity and prevalence of prediabetes and T2DM adjusting for potential confounders such as time since HIV diagnosis, age, gender, and lack of housing. For participants in the longitudinal cohort without prediabetes or T2DM at baseline, we will use survival models for interval-censored data to compare incidence rates between food-secure and food-insecure participants. We will use survival methods for interval-censored data because the exact date of progression to prediabetes or T2DM is unknown but occurs between two assessment dates. In addition, this technique does not need to account for loss to follow-up since it uses models that make use of all available data for those lost to follow-up. We will estimate and compare incidence rates for food-secure and food-insecure participants using the non-parametric survival analysis procedure in SAS PROC ICLIFETEST.

The two groups will be compared with a weighted generalized log-rank test. Next, we will fit proportional hazards regression models for interval-censored data using PROC ICPHREG that will allow us to adjust for potential confounders and include time-varying covariates. Participants will be included in the analysis up until the end of their follow-up (the last time they have an in-person visit) or the first visit in which they are diagnosed with prediabetes or T2DM. For individuals diagnosed with prediabetes at baseline or during the follow-up, we will estimate the incidence of transitioning to diabetes using similar survival models. We will explore the prevalence and incidence of other secondary cardiometabolic comorbidities using similar analyses. We will also use linear mixed effects regression models to estimate trends in A1C and other continuous indicators of cardiometabolic comorbidities (secondary outcomes) over time accounting for the correlation of repeated measures using a random intercept model. We will test for difference in trends (slopes) between food-secure and insecure individuals using *F*-tests. These models will be fit using SAS PROC MIXED.

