#### Aim 2: Implement and test weCare/Secure to determine the impact of the intervention on insulin sensitivity among food-insecure PWH with prediabetes or T2DM using an RCT

##### Participants

The participants in Aim 2 will be a subset of Aim 1 participants who enrolled in year 1. From potentially eligible participants identified by EHR data extracted in Aim 1, we will randomly select participants to invite to enroll in Aim 2, starting in year 2. To be eligible to participate in Aim 2, a participant must (a) be a patient of the Wake Forest Infectious Diseases Specialty Clinic, (b) be living with HIV, (c) be receiving antiretroviral therapy (ART) for ≥ 3 months, (d) be ≥18 years of age, (e) screen as food insecure, (f) have prediabetes or T2DM, and (g) provide informed consent. Access to a smartphone will not be an inclusion criterion because participants may communicate with the peer navigator via mHealth platforms accessible on a computer (e.g., Facebook messenger) at their home or in community spaces such as the public library. PWH will be excluded if they are unable to speak English or Spanish, are currently pregnant, are receiving chronic treatment with systemic corticosteroids (similar exclusion as the Look AHEAD Trial, which evaluated the effects of an intervention designed to promote weigh loss among overweight and obese individuals with T2DM [57]), have type 1 diabetes, and/or have cognitive impairment that would prevent participation.

If participants are eligible and consent to participate, they will then complete Aim 2 baseline data collection as outlined in Table 1. After these data are collected, they will be randomly assigned into weCare/Secure (*n*=100) or usual care (*n*=100). Those randomized to the weCare/Secure intervention will receive the intervention for 6 months. For random selection and assignment, our statistician will use block randomization with a randomly selected block size. The research coordinator will enroll, consent, and assign participants to groups. We will continue this process until we reach our sample size of 200. Participants may discontinue participation in the intervention at any time. Given the behavioral nature of the intervention, there will be no other special criteria for discontinuing or modifying allocated interventions. Aim 2 participants will be compensated $40 at baseline and $60 at 6-month follow-up.

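### The Aim 1 case rule counts type 1 diabetes as T2DM and lets one person meet both the prediabetes and T2DM definitions, which affects baseline prevalence, the separate prediabetes estimate and the transition analysis

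*Protocol article*

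**What the plan says.** The case rule stands under Aim 1, Data collection.

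- **Primary outcome.** "The primary outcome for Aim 1 is prediabetes or T2DM", a composite.
- **Prediabetes.** A "clinical diagnosis of prediabetes if they have a hemoglobin A1C level ≥ 5.7% and < 6.5% measured at the time of the clinic visit". Nothing requires that the T2DM criteria be absent.
- **T2DM.** "A participant will be determined to have T2DM if they have any one of the following: an A1C ≥ 6.5"%, a prior T2DM history by ICD-10 code, or "currently taking a diabetic medication (including glucagon-like peptide 1 receptor agonist, sodium-glucose cotransporter 2 inhibitor, dipeptidyl peptidase 4 inhibitor, sulfonylurea, incretin mimetic, or insulin". Each limb suffices alone.
- **Aim 1 exclusions** (Aim 1, Participants). "PWH will be excluded if they are unable to speak English or Spanish or have cognitive impairment that would prevent participation". Type 1 diabetes is not named.
- **Aim 2 exclusions** (Aim 2, Participants). The list adds those who "have type 1 diabetes, and/or have cognitive impairment that would prevent participation".
- **Incidence analysis** (Analysis plan for Aim 1). "For participants in the longitudinal cohort without prediabetes or T2DM at baseline, we will use survival models for interval-censored data". Follow-up ends at the last in-person visit or the first visit with either diagnosis.
- **Component analyses** (same section). Prevalence of prediabetes and of T2DM is estimated in each food-security group. Progression to diabetes is estimated in people with prediabetes at baseline or during follow-up. The power section also treats the two incidence rates separately.

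**The concern.** The protocol gives a complete rule with explicit connectives, so it can be applied as written. Doing so produces three kinds of wrong label.

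1. A participant with type 1 diabetes who takes insulin, or whose A1C is at least 6.5%, is labelled T2DM. The Aim 2 exclusion shows that the investigators meant to keep type 1 apart there.
2. A participant with treated or coded T2DM whose A1C is, say, 6.0% is both prediabetic and diabetic. No precedence is stated.
3. A participant with normal A1C and no diabetes code who starts a listed drug becomes an incident T2DM case on the prescription alone.

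At stake are the baseline prevalence comparison, the separate prediabetes and T2DM estimates, and the transition analysis, whose risk set should hold only people who do not yet have diabetes.

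**Working it through.** **Step 1. The plan's own figure.** Inputs from Power and sample size for Aim 1: 1260 food-secure and 540 food-insecure participants, prevalence 25% against 31.6%, two-sided 5% test.

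- Pooled proportion: (1260 × 0.25 + 540 × 0.316)/1800 = 0.2698.
- SE under the null: √[0.2698 × 0.7302 × (1/1260 + 1/540)] = 0.0228.
- SE under the alternative: √[0.25 × 0.75/1260 + 0.316 × 0.684/540] = 0.0234.
- Power: Φ[(0.066 − 1.96 × 0.0228)/0.0234] = Φ(0.907) = 0.818.

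The stated 80% reproduces.

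**Step 2. The rule applied to four kinds of participant.**

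| Participant | Label under the rule | Where it matters |
|---|---|---|
| Established type 1, on insulin | T2DM at baseline | Baseline prevalence, composite and T2DM. Leaves the incidence risk set |
| Treated or coded T2DM, A1C 6.0% | Prediabetes and T2DM | Separate prediabetes estimate and transition risk set. Counted once in the composite |
| Normal A1C, no code, starts a listed drug in follow-up | Incident T2DM | T2DM incidence and the composite |
| New-onset type 1 in follow-up | Incident T2DM | T2DM incidence and the composite |

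The second row does not alter the composite because prediabetes-or-T2DM is a union. It does alter the transition analysis: that person enters as prediabetic while already satisfying the endpoint.

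**Step 3. Baseline false positives.** The protocol gives no type 1 or off-indication rate, so the proportion q of true non-cases labelled as cases is assumed. Each prevalence p becomes p + (1 − p)q.

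| q | Extra cases | Power |
|---|---|---|
| 0 | 0 | 0.818 |
| 0.5% | 7 | 0.811 |
| 1% | 13 | 0.804 |
| 2% | 26 | 0.791 |
| 5% | 66 | 0.749 |

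**Step 4. False incident events from a drug alone.** Stated rates are 13.7 (T2DM) and 125 (prediabetes) per 1000 person-years. I take their sum, 138.7, as the composite rate. The false-event rate f is assumed, equal in both groups, with the same exposure for true and false events. The last column starts from the plan's ratio of 3.7, with 13.7 as the food-secure rate, so the food-insecure rate is 13.7 × 3.7 = 50.69 and the observed ratio is (50.69 + f)/(13.7 + f).

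| f per 1000 PY | Share of T2DM-only events, f/(13.7 + f) | Share of composite events, f/(138.7 + f) | Observed T2DM ratio |
|---|---|---|---|
| 2 | 2/15.7 = 13% | 2/140.7 = 1.4% | 3.36 |
| 5 | 5/18.7 = 27% | 5/143.7 = 3.5% | 2.98 |
| 10 | 10/23.7 = 42% | 10/148.7 = 6.7% | 2.56 |

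Even at f = 10, power to detect some difference in T2DM incidence stays at 0.999 over three years without loss (1350 at risk, 30% food insecure). The harm is a biased T2DM rate and ratio, not a loss of power.

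**The case against.** The strongest defence has four parts.

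- **The composite is robust to the overlap.** This stands. The point is confined to component and transition analyses.
- **Established type 1 cases leave the incidence risk set.** This stands too. Their effect is on baseline prevalence.
- **The wording already favours T2DM, and the drug limb can be read as a drug taken for diabetes.** The any-one-of wording does suggest that T2DM governs, but precedence is not stated, and the transition analysis admits anyone diagnosed with prediabetes. The drug limb lists classes and states no indication test.
- **An article condenses the full protocol, and ICD-10 codes are extracted, so type 1 could be separated later.** This explains missing detail. It does not cover a rule that is stated in full and gives wrong labels when followed.

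A reader might infer more: that incident T2DM will be misclassified on a large scale, or that the error differs between food-secure and food-insecure participants because drug access follows insurance and obesity. The documents do not support either. They do not mention use of these drugs outside diabetes, give no frequency, and do not link insurance or obesity to receipt of the drugs. The 27–42% is conditional on an assumed rate and refers to T2DM-only events, not to the primary outcome.

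**Conclusion.** The concern holds in a limited form. Two defects follow from the text without outside assumptions: type 1 diabetes is counted as T2DM in Aim 1 although Aim 2 excludes it, and prediabetes and T2DM overlap without a precedence rule. The first affects baseline prevalence. The second can inflate the separate prediabetes estimate and contaminate the transition risk set. The documents do not give the number of people involved in either, so their size cannot be computed. The effect on prevalence power is modest: 0.804 against 0.818 if 1% of non-cases were mislabelled.

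The third defect, an incident event created by a drug alone, is possible under the rule and would reach the composite. Its size rests wholly on an assumed rate: 27–42% of T2DM-only events and 3.5–6.7% of composite events at 5 to 10 per 1000 person-years, and proportionately less at lower rates. It warrants a sensitivity analysis rather than a new primary definition.

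**What to change.** 1. Use the ICD-10 codes already extracted (Table 1) to remove participants with type 1 diabetes from the Aim 1 outcome analyses.
2. Define prediabetes as A1C 5.7% to <6.5% with no T2DM criterion met, and restrict the transition-to-diabetes risk set to people who meet that definition.
3. Add a sensitivity analysis in which medication use alone, without a T2DM code or A1C ≥6.5%, does not count as T2DM.

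I would not make item 3 the primary rule. Requiring a drug to be accompanied by a code or a qualifying A1C is the same as deleting the medication limb, since either already suffices. Checking the indication on the order is not an available substitute, because Table 1 does not list that item.

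The cost is a little more work on the EHR case definition and one extra analysis; no new data are needed. The sensitivity analysis may miss some people with treated, well-controlled, uncoded T2DM, which should be said when it is reported.

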## Trial status

Aim 1 (longitudinal cohort) recruitment began in May 2022 and is ongoing. Aim 2 (intervention) recruitment is planned for spring 2023 and is expected to be completed in spring 2024. Aim 3 (process evaluation) data collection will occur after sufficient completion of the 6-month assessment in Aim 2. Final results are anticipated in fall 2025.

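### Aim 1's detectable incidence rate ratios of 1.7 (prediabetes) and 3.7 (T2DM) do not follow from the protocol's own inputs; the error is conservative

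*Protocol article*

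**What the plan says.** All inputs stand in the protocol article, under *Power and sample size for Aim 1* unless noted.

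- Cohort: 1800 patients, 30% assumed food insecure, followed for up to 3 years with 15% lost.
- At risk: 1350 people, a figure introduced with "Assuming that 75% of the sample will not have prediabetes/T2DM at baseline, the sample size for estimating incidence is".
- Rates: "we assume the incidence of prediabetes is 125 per 1000 person-years and the incidence of T2DM is 13.7 per 1000 person-years". The text does not say whether these apply to the food-secure group or to the whole cohort.
- Claim: "We then have 80% power to detect a prediabetes incidence rate ratio of 1.7 between those with and without food insecurity". For T2DM the corresponding ratio is put at 3.7, and both figures are tied to a two-sided 5% log-rank comparison.
- Visits (*Data collection*, Aim 1): "data will be collected at baseline and at 12-, 24-, and 36-month follow-up".
- End of follow-up in the incidence analysis (*Analysis plan for Aim 1*): the last in-person visit or "the first visit in which they are diagnosed with prediabetes or T2DM". The same section then plans a separate analysis of transition to diabetes among people with prediabetes at baseline or during follow-up.

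No follow-up shorter than 3 years is given for the power calculation.

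**The concern.** A rate of 125 per 1000 person-years in 1350 people over 3 years yields several hundred prediabetes events. A log-rank test with a 30:70 split needs only about 133 events for 80% power at a ratio of 1.7. The stated ratios therefore look too large for the stated design.

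Incidence is half of the Aim 1 objective, and this is its only power statement. As written, it tells the reader that the cohort reaches 80% power only at a 1.7-fold or 3.7-fold rate. If less person-time was assumed, that assumption is not disclosed.

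**Working it through.** **A neighbouring figure first.** The baseline prevalence claim in the same section (25% vs 31.6%) does reproduce: 1260 vs 540 participants give 81.8% power with pooled variance. The problem is confined to the incidence sentence.

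**Groups.** 0.70 × 1350 = 945 food secure; 0.30 × 1350 = 405 food insecure.

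**Events needed (Schoenfeld).** d = (1.96 + 0.84)² / (0.3 × 0.7 × ln(RR)²) = 7.85 / (0.21 × ln(RR)²).
- RR 1.7: 7.85 / (0.21 × 0.5306²) ≈ 133
- RR 3.7: 7.85 / (0.21 × 1.3083²) ≈ 22

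**Events expected over 3 years.** Take the quoted rates as food-secure and remove 15% from each group, leaving 803.25 and 344.25. Events per group are n × (1 − e^(−3λ)).
- Prediabetes at RR 1.7: 803.25 × (1 − e^(−0.375)) + 344.25 × (1 − e^(−0.6375)) = 251.2 + 162.3 ≈ 413
- T2DM at RR 3.7: 803.25 × (1 − e^(−0.0411)) + 344.25 × (1 − e^(−0.1521)) = 32.3 + 48.6 ≈ 81

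**Power at the stated ratios**, Φ(√(0.21 d) × ln RR − 1.96):
- Prediabetes: Φ(4.94 − 1.96) ≈ 99.9%
- T2DM: Φ(5.39 − 1.96) > 99.9%

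**Ratios detectable at 80% power over 3 years.** These solve expected events = required events. The ranges run over no loss, 15% loss as exponential censoring, and 15% removed from N. In the whole-cohort reading, the food-secure rate is λ / (0.7 + 0.3 RR).

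| Reading of the rates | Formula | Prediabetes | T2DM |
|---|---|---|---|
| Food-secure group | Schoenfeld | 1.33-1.36 | 2.07-2.18 |
| Food-secure group | Freedman | 1.31-1.34 | 1.94-2.04 |
| Whole cohort | Schoenfeld | 1.35-1.38 | 2.30-2.46 |
| Whole cohort | Freedman | 1.33-1.36 | 2.11-2.24 |

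The lowest power at the stated ratios in any of these cells is about 98% (T2DM, whole cohort, Schoenfeld, 15% off N). Placing the rates in the food-insecure group moves T2DM to 3.14-3.57 (Schoenfeld) but leaves prediabetes at 1.36-1.43, so the pair is still not reproduced.

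**Annual visits.** A simulated log-rank test on yearly assessments (2000 runs, 3 years, 15% loss, rates as food-secure) gave power of 99.9% at 1.7, 100% at 3.7, 82% at 1.35 for prediabetes and 83.6% at 2.1 for T2DM. Grouped assessment does not explain the gap.

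**Staggered follow-up.** If follow-up is uniform over 0-3 years, events per group are n × (1 − (1 − e^(−3λ)) / (3λ)). With 15% off N and Schoenfeld, the food-secure reading gives 1.52 and 2.80. The whole-cohort reading gives 1.56 and 3.57, which brings T2DM near 3.7 but not prediabetes near 1.7.

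**T2DM with follow-up stopped at prediabetes.** With prediabetes at 125 per 1000 person-years also ending follow-up (independence assumed, 15% censoring, 3 years), T2DM events at a common rate fall from about 50 to about 42. The detectable ratio becomes about 2.1-2.6.

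**The case against.** The strongest reply is that follow-up is described only as lasting up to 3 years, recruitment opened in May 2022 and was ongoing, and "Final results are anticipated in fall 2025" (*Trial status*). Full 3-year person-time may never have been the planned exposure, and the right replacements may be larger than 1.35 and 2. That stands, and it is why the fix asks for the person-time rather than prescribing figures. It does not rescue the sentence, because even evenly spread follow-up leaves prediabetes at about 1.5-1.6.

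It can also be said that nothing depends on the error: Aim 1 is an observational cohort taking in about 90% of the clinic, the mistake understates its power, and the randomised Aim 2 is untouched. All of that is right and limits the weight of the point. What a null result is compatible with will come from the observed confidence interval, not from this sentence.

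Three stronger readings are tempting, and the document does not support them.
- **That one year of follow-up was used.** The follow-up that returns the stated ratios runs from roughly 0.5 to 1.4 years across formulas and the food-secure and whole-cohort readings, so no single cause can be named.
- **That the T2DM figure has no matching analysis.** T2DM without a preceding prediabetes diagnosis stays in the analysis of the 1350, and progression from prediabetes has its own planned analysis. The document only leaves open which of the two the 3.7 belongs to.
- **That the calendar contradicts the follow-up.** Follow-up of up to 3 years allows less for later enrolees, and the interval-censored models use whatever is available.

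**Conclusion.** The stated pair of ratios is wrong for the stated inputs. With full 3-year follow-up the 80%-power ratios are about 1.31-1.38 for prediabetes and 1.9-2.5 for T2DM, and power at 1.7 and 3.7 is about 98% or more. This rests on constant hazards, the 30% split carrying over to the 1350, and the rates describing either the food-secure group or everyone. No variant tried with the stated sample, split, rates and 3 years returns both figures.

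A reader might infer that incidence in Aim 1 is underpowered. The opposite holds: on the stated assumptions the cohort can detect smaller ratios than claimed. This is a reporting error worth correcting because it is cheap to correct, not a design flaw.

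**What to change.** In *Power and sample size for Aim 1*:

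1. State the person-time or follow-up distribution assumed, how the 15% loss enters, and whether the quoted rates are for the food-secure group or the whole cohort.
2. Restate both detectable ratios for that person-time. Under full 3-year follow-up they would be about 1.31-1.38 and 1.9-2.5.
3. Say which analysis the T2DM ratio refers to: the one in the 1350, where follow-up ends at the first diagnosis of either condition (fewer T2DM events, so a slightly larger ratio), or the prediabetes-to-diabetes transition analysis, which has a different risk set and needs its own numbers.

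The cost is one recalculation and a few sentences. Sample size, visits and planned analyses stay as they are. Redefining the T2DM population would be a choice of estimand and is not needed to correct this.
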